### Statistical analyses and power

The primary outcomes are changes in children’s self-regulation, which will be analyzed in multi-level models where a specific intervention-control comparison will be included. The analyses will be carried out using two different types of dataset: intention-to-treat*,* including all participants according to the random allocation, irrespective of whether the intervention was implemented with fidelity (to estimate program effects if implemented more broadly); and per-protocol, including all participants for which the program was implemented to the minimum requirements described in the “PRSIST Program intervention” section (to estimate program effects if implemented with fidelity).

To evaluate the effect of the PRSIST Program intervention, changes in child outcomes will first be measured in a multi-level model where a specific intervention-control comparison will be included. Based on an ICC of .12 and a small effect size, 500 participants will be sufficient to detect a child-level effect at 80% power, alpha of .05 and 10% attrition. For educator-level data, based on an ICC of .05 and a moderate effect size, 120 participants (at least two educators per center) will be sufficient to detect this effect at 80% power and alpha of .05. These ICCs were anticipated on the basis of previous large-scale research in children clustered within different preschool settings [23], and anticipated effect sizes were based on initial small-scale piloting of this approach to promoting self-regulation [17]. Multiple imputation methods will be used for missing individual outcome data. Covariates to be considered in the analyses include the NQS, child age, child sex, maternal education and socioeconomic status.

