**Methods/design:**

The Early Start to Self-Regulation study is a cluster randomized, controlled trial for evaluating benefits of the Preschool Situational Self-Regulation Toolkit (PRSIST) program, when implemented by early childhood educators, compared with routine practice. The PRSIST program combines professional learning, adult practices, child activities and connections to the home to support children’s self-regulation development. Fifty preschool centers in New South Wales, Australia, will be selected to ensure a range of characteristics, namely: National Quality Standards (NQS) ratings, geographic location and socioeconomic status. After collection of baseline child and educator data, participating centers will then be randomly allocated to one of two groups, stratified by NQS rating: (1) an intervention group (25 centers) that will implement the PRSIST program; or (2) a control group (25 centers) that will continue to engage in practice as usual. Primary outcomes at the child level will be two measures of self-regulation: Head-Toes-Knees-Shoulders task and the PRSIST observational assessment. Secondary outcomes at the child level will be adult-reported measures of child self-regulation, executive function and school readiness. Outcomes at the educator level will involve a survey of their perceived knowledge, attitudes and self-efficacy for supporting children’s self-regulatory development. In all cases, data collectors will be blinded to group allocation.

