### Child characteristics and recruitment

Following center recruitment, and preceding the intervention, children in the final preschool year (4–5 years of age) will be recruited from participating centers. This involves circulating information sheets and consent forms, via the center, to parents or legal guardians of suitably aged children. Participating children will be those that meet the age-inclusion criteria, return a signed parental consent form and provide verbal assent to participate. Fifty preschool centers are expected to yield a sample of approximately 500 children ages 4–5 years, with whom the child assessments will be conducted. There are no further exclusion criteria for child participation.

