### Randomized allocation of centers

After baseline data collection is completed, all participants (i.e., educators and children) will be assigned to control or intervention groups randomly by cluster (center) using a computer-generated random number sequence. Randomization will not occur until after: (a) recruitment of centers is complete; and (b) initial baseline data collection is complete. As such, those involved in recruitment of centers will be unaware, at the time of recruitment, to which group centers will be allocated. Stratified randomization of centers (cluster) will be conducted using NQS rating as the core stratification variable.

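### If small means 0.2 SD, the stated design has about 33% power unadjusted (42% to 56% with plausible baseline adjustment), not the 80% claimed for the child-level outcomes

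*Protocol article*

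**What the plan says.** The protocol article, under Statistical analyses and power, states: "Based on an ICC of .12 and a small effect size, 500 participants will be sufficient to detect a child-level effect at 80% power", and the sentence ends with "alpha of .05 and 10% attrition". On the source of the effect it says only that "anticipated effect sizes were based on initial small-scale piloting of this approach to promoting self-regulation". No value in SD units is given, nor whether alpha is one- or two-sided, nor any correlation between baseline and post-test.

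The other inputs are stated elsewhere in the article:

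- **Sample** (Child characteristics and recruitment): "Fifty preschool centers are expected to yield a sample of approximately 500 children".
- **Arms** (Abstract, Methods/design): "an intervention group (25 centers) that will implement the PRSIST program" and "a control group (25 centers) that will continue to engage in practice as usual".
- **Unit of allocation** (Randomized allocation of centers): groups are assigned "randomly by cluster (center) using a computer-generated random number sequence".

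The same power paragraph describes the primary outcomes as changes in self-regulation analysed in multi-level models. It lists NQS, age, sex, maternal education and socioeconomic status as candidate covariates. Outcome measures and procedures has every measure taken at baseline and at post-test.

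**The concern.** The power sentence is the article's only justification for the number of children behind both primary outcomes (HTKS and the PRSIST assessment). With an ICC of .12 and about 9 analysed children per center, clustering roughly halves the information in the sample. What remains looks too little for an effect that would ordinarily be called small.

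The interpretation of the result is at stake. A reader who accepts 80% power for a small effect would give a non-significant primary result more weight against such an effect than the design supports.

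**Working it through.** **Inputs from the article.** 50 centers, 25 per arm; about 500 children, so 10 per center; 10% attrition, so 450 analysed, 9 per center; ICC .12; alpha .05.

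**Assumptions.** Alpha is two-sided. Small is 0.2 SD, with a range shown. Centers are of equal size; unequal sizes would lower power further.

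**Step 1. Design effect.** DE = 1 + (9 − 1) × .12 = 1.96. Effective sample = 450 / 1.96 ≈ 230.

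**Step 2. Standard error of the difference in SD units.** SE = √(4 × 1.96 / 450) = 0.132.

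**Step 3. Where the article's 80% is reproduced.** Detectable effect = (1.96 + 0.84) × 0.132 ≈ 0.37 SD, or 0.38 SD using t with 48 degrees of freedom. Without adjustment, the stated 80% therefore corresponds to 0.37 SD.

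**Step 4. Power at 0.2 SD.** 0.2 / 0.132 = 1.515, and Φ(1.515 − 1.96) = 33%. A t test on 48 degrees of freedom gives 31.7%, as does a simulation of 50 center means.

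**Step 5. Other effect sizes, same design, unadjusted.**

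| Effect (SD) | Power |
|---|---|
| 0.20 | 33% |
| 0.25 | 47% |
| 0.30 | 62% |
| 0.35 | 76% |
| 0.37 | 80% |
| 0.40 | 86% |

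**Step 6. Can another reading of the stated inputs give 80% at 0.2 SD without adjustment?**

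- No attrition (500 children, 10 per center, DE 2.08): 34%.
- One-sided alpha: 45%.
- Unlimited children in each of the 50 centers: SE = √(4 × .12 / 50) = 0.098, power 53%.
- Clustering ignored: 56% with 450 children, 61% with 500.

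None does. For scale, 80% power at 0.2 SD without adjustment takes 786 × 1.96 ≈ 1,541 analysed children, at 9 per center.

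**Step 7. Baseline adjustment.** With pre-post correlation r, taken as equal at both levels, SE is multiplied by √(1 − r²).

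| Assumed r | Power at 0.2 SD | Effect detectable at 80% |
|---|---|---|
| .5 | 42% | 0.370 × 0.866 = 0.32 SD |
| .6 | 47% | 0.370 × 0.800 = 0.30 SD |
| .7 | 56% | 0.370 × 0.714 = 0.26 SD |

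At r = .8, power at 0.2 SD is 71%. An unadjusted analysis of raw change at r = .5 gains nothing, because the variance of change is 2(1 − .5) = 1 times the outcome variance; power stays at 33%.

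**Step 8. Covariate strength needed for 80% at 0.2 SD.** With equal R² at both levels, R² = 1 − (0.2 / 0.370)² ≈ .71, a correlation of about .84. Other combinations also work. With SE² = (4/50)[.12(1 − R²center) + .88(1 − R²child)/9], taking .80 at center level and .59 at child level gives SE² = .08 × (.0240 + .0401) = .00513, SE = 0.072 and power of about 80%.

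**The case against.** The strongest reply is that the decisive input is not in the document. The article gives no number for the effect and refers to a pilot that is not at hand; 0.2 SD is a convention brought in from outside. This stands, so every figure at 0.2 SD is conditional on that reading. The convention is still the natural one: the same paragraph uses small for children and moderate for educators. At 0.5 SD the educator figure (120 participants, ICC .05, 2.4 per center, DE 1.07) comes to about 75%, near its claimed 80%. The child figure at 0.2 SD does not come near.

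Second, the planned outcome is change, with a baseline measure available, so the 33% does not describe the analysis intended. This also stands in part. A target of 0.3 SD with baseline adjustment at r = .6 gives 81%, and 0.3 SD could loosely be called small. A repeated-measures calculation with Cohen's f = 0.10 and correlation .5 gives 84% to 86%, but it implies a difference in change of about 0.4 SD. Each route rests on inputs that the article does not state.

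Third, a condensed article may leave such inputs to a fuller document. That would excuse silence about details. It does not settle whether a printed power figure agrees with the inputs printed beside it.

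A reader might infer more than the document supports:

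- **That 80% for a small effect is impossible.** It is not shown to be, because small is undefined and adjustment is open.
- **That the trial has only a one-in-three chance of success.** That figure combines 0.2 SD with an unadjusted comparison.
- **That 53% is an absolute ceiling, or that R² of .71 at both levels is required.** The first holds only if no center-level variance is explained; the second is one solution among several.
- **That the investigators will read a null result as excluding a small effect.** The article does not say so.

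**Conclusion.** The concern holds in conditional form. Taking small as 0.2 SD, with two-sided alpha and equal center sizes, the stated design has about 33% power unadjusted and about 42% to 56% with baseline adjustment at an assumed correlation of .5 to .7. The claimed 80% is not delivered at that effect size. It corresponds to about 0.37 SD unadjusted, nearly twice the conventional small value, or to a smaller effect only with an adjustment gain that the power statement does not mention. The arithmetic is firm given the inputs; what is uncertain is the effect size and baseline correlation the investigators had in mind. If these were used but not printed, disclosing them would resolve the point.

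**What to change.** Rewrite the child-level power sentence and leave enrolment unchanged. State the target effect in SD units, the expected number of children per center, whether alpha is two-sided, and any baseline correlation or covariate gain assumed. For example:

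*With 25 centers per arm, about 450 children analysed (9 per center), ICC .12 and two-sided alpha .05, the trial has 80% power to detect about 0.37 SD without adjustment. With adjustment for the baseline score, the detectable effect is about 0.32 SD or 0.26 SD if the pre-post correlation is .5 or .7 (assumed values). Power for 0.2 SD without adjustment is about 33%.*

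The correlations of .5 and .7 are illustrations, not values from the article, and should be replaced by whatever the investigators can support. The change costs one reworded paragraph and a less favourable stated figure; the design and the analysis stay as they are.

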### Outcome measures and procedures

All measures will be administered at baseline and again after the 6-month intervention period (post-test). The battery of child measures was selected to include multi-source measures of children’s self-regulation (objective, observational, educator-report, parent-report) and related abilities. In total, the child measures involve approximately 60 minutes of direct assessment per child (split into three sessions of 20 minutes each) and around an hour of educator time per center (5 minutes of educator time per child for the educator-report self-regulation measure, and 15 minutes to complete a survey of educators’ perceived self-regulation knowledge, attitudes and self-efficacy). In all cases, a trained fieldworker will carry out child assessments in a quiet area of the child’s preschool center. In all cases, fieldworkers collecting the baseline and outcome data will be blinded to each center’s group allocation.

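### The primary outcome is change, but neither the baseline score nor the NQS stratum is fixed in the primary model; fixing both would usually gain precision at no data cost

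*Protocol article*

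**What the plan says.** Under Statistical analyses and power, the protocol article states: "The primary outcomes are changes in children’s self-regulation, which will be analyzed in multi-level models where a specific intervention-control comparison will be included". It adds that "changes in child outcomes will first be measured in a multi-level model where a specific intervention-control comparison will be included". It does not say whether change is a subtracted score or a time effect in a repeated-measures model.

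On covariates, the same section says: "Covariates to be considered in the analyses include the NQS, child age, child sex, maternal education and socioeconomic status". Five variables are named and the baseline score of the outcome is not one of them. The list is not declared complete.

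Two other sections bear on this. Outcome measures and procedures says "All measures will be administered at baseline and again after the 6-month intervention period (post-test", so a baseline score is planned for every outcome. Randomized allocation of centers says "Stratified randomization of centers (cluster) will be conducted using NQS rating as the core stratification variable". The design therefore commits to NQS, while the analysis text gives it the same tentative status as maternal education.

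**The concern.** Two readings of change come first to mind: a subtracted score, or a group-by-time model in which the arms' baseline means are free to differ. With complete data both estimate the same contrast, the difference between arms in mean change. That contrast in effect fixes the slope of post-test on baseline at 1. When the true slope is below 1, the change score over-corrects for any chance baseline difference (regression to the mean) and carries more noise than necessary. With 25 centers per arm, chance baseline differences are to be expected.

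The stratum raises a related issue. If NQS rating predicts the outcome and is left out of the model after stratified randomization, the standard error is generally too large. Both variables are already to be collected, so any precision lost this way is lost for nothing.

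**Working it through.** **Inputs from the protocol article**
- ICC and effect: "Based on an ICC of .12 and a small effect size". No number is given for the effect.
- Sample: "500 participants will be sufficient to detect a child-level effect at 80% power, alpha of .05 and 10% attrition", so 450 children analysed.
- Clusters: "Fifty preschool centers are expected to yield a sample of approximately 500 children ages 4–5 years", so about 10 children per center, or 9 after attrition; 25 centers per arm.

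**Assumptions (not in the article)**
- Two-sided alpha; d = 0.20 for a small effect, with 0.30 shown as well.
- Pre-post correlation r from .3 to .8, at first equal at child and center level; equal variances at the two time points; effects in post-test SD units.

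**Step 1: the plan's own figure.** Design effect = 1 + (9 − 1) × 0.12 = 1.96. Effective sample = 450 / 1.96 ≈ 230. Without credit for baseline, the effect detectable with 80% power is (1.960 + 0.842) × √(2 × 1.96 / 225) = 0.37 SD. At d = 0.20 power is 33% (34% with all 500 children at 10 per center; 45% one-sided with 450), and at d = 0.30 it is 62%. The stated 80% is not reproduced at d = 0.20.

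**Step 2: change against baseline adjustment.** Relative to an unadjusted post-test comparison, the variance is 2(1 − r) for change and 1 − r² with baseline adjustment. The ratio is (1 − r²) / [2(1 − r)] = (1 + r)/2. Detectable effects are 0.370 times the square root of each variance; power uses the same variances.

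| r | Ratio | Detectable effect, change | Detectable effect, adjusted | Power at d = 0.20 (change / adjusted) | Power at d = 0.30 (change / adjusted) |
|---|---|---|---|---|---|
| .3 | 0.65 | 0.44 | 0.35 | 25% / 36% | 48% / 66% |
| .5 | 0.75 | 0.37 | 0.32 | 33% / 42% | 62% / 75% |
| .6 | 0.80 | 0.33 | 0.30 | 40% / 47% | 72% / 81% |
| .7 | 0.85 | 0.29 | 0.26 | 50% / 56% | 84% / 89% |
| .8 | 0.90 | 0.23 | 0.22 | 67% / 71% | 95% / 97% |

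Below r = .5, 2(1 − r) exceeds 1, so change is less precise than the post-test alone. To reach 80% at d = 0.20, r must be about .84 with baseline adjustment and about .85 with change.

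**Step 3: unequal correlations.** Let center means be more stable than individual scores: r = .5 within centers and .9 between centers (illustrative values). For a single slope b, the variance of an adjusted center mean is 0.12(1 + b² − 1.8b) + (0.88/9)(1 + b² − b).
- Change (b = 1): 0.0240 + 0.0978 = 0.1218.
- b = .50: 0.0420 + 0.0733 = 0.1153, a saving of 5%.
- b = .55: 0.0375 + 0.0736 = 0.1111, a saving of 9%.

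The overall r is 0.12 × .9 + 0.88 × .5 = .548, for which (1 + r)/2 would have promised a saving of 23%. With a between-center correlation of 1, change gives 0.0978 and b = .50 gives 0.12 × 0.25 + 0.0733 = 0.1033. One pooled slope can therefore do worse than change.

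Adding the center-mean baseline lets the between-center slope be estimated separately. The relevant correlation is then that of observed center means: R = (0.12 × .9 + 0.0978 × .5) / (0.12 + 0.0978) = 0.1569 / 0.2178 = .72. The ratio is (1 + .72)/2 = 0.86, a saving of 14%, before the small cost of estimating one more slope from 50 centers.

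**Step 4: the stratum.** The article gives no figure for how strongly NQS rating predicts the outcomes, so the gain from fixing it in the model cannot be calculated.

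**The case against.** The strongest reply is that the article does not commit to the weaker analysis. Change analysed in a multi-level model could be a longitudinal model with baseline means constrained equal, or a baseline-adjusted post-test model reported as change. The covariate list is open and NQS is the first variable on it. A condensed article commonly leaves the model equation to an analysis plan, and that plan is not shown. All of this stands. A reader might infer that the trial will certainly waste precision, will omit the stratum, or will choose covariates after seeing the data; the text supports none of these. What remains is that the article does name an outcome form and does name covariates, and what it names leaves out the baseline score and leaves the stratum uncommitted.

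A second reply is that a change analysis is sound under randomization: it is unbiased over repeated allocations and keeps its type I error when clustering is modelled, as planned. That also stands. Sensitivity to imbalance is conditional on the allocation actually drawn and is no systematic bias. Omitting the stratum would generally make inference conservative, not invalid.

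Third, the size of the gain depends on an unstated r and on its being equal at both levels. Step 3 bears this out, so it would be too strong to say that change can never be the more precise choice.

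**Conclusion.** The point holds as an efficiency and prespecification improvement. As written, the primary analysis centers on change, does not name the baseline score, and leaves NQS optional. On the subtracted-score or unconstrained group-by-time reading, baseline adjustment saves about 35% to 10% of variance for r from .3 to .8. That is roughly 4 to 11 percentage points of power at d = 0.20. These figures assume equal r at child and center level, ICC .12 and 450 children analysed. With much more stable center means, the saving from one pooled slope falls to about 5 to 9% in the example and can vanish.

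A reader might also infer that this choice explains a power shortfall, or that correcting it would deliver the stated 80%. Neither follows. The small effect has no number, so the shortfall depends on taking d = 0.20. At that value baseline adjustment reaches 80% only if r is about .84. Power is a separate and larger question.

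**What to change.** Define the primary model for each child outcome, for example: a mixed model of the post-test score with a random effect for center and, as prespecified fixed terms, arm, the child's baseline score on that outcome, the center-mean baseline score, and NQS stratum. The center-mean term avoids forcing one slope on both levels. An equivalent longitudinal model with the arms' baseline means constrained equal, and NQS stratum included, would serve as well. Report change descriptively.

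The roles of maternal education and socioeconomic status can stay as the investigators prefer; moving them to a sensitivity analysis is optional and not part of this change.

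The cost is a few sentences of analysis text. All the variables are already to be collected, and the design, sample and procedures are unaffected.

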### Ethical and research governance approval

The study was granted ethical approval by the University of Wollongong Human Research Ethics Committee Social Sciences (HE2017/451) on 7 November 2017. Written consent will be obtained from Center Directors (for center participation), educators (for participation and completion of educator-report measures), and children’s parent(s) or legal guardian(s) as a condition for participation. This will include consent for publication of the study results in anonymized aggregate format. Per the Consolidated Standards of Reporting Trials (CONSORT) guidelines, the study’s final reporting will follow the CONSORT statement and its relevant extensions (e.g., cluster trials, non-pharmacological interventions).

### Study timeline

Recruitment of centers will commence in January 2018 and recruitment of children will begin in February 2018. Pre-test data will be collected in March and April 2018, with post-test data collected 7 months after pre-test in October and November 2018. Figure 1 provides details of the stages of the study. The trial is set to finish in December 2018.

## Discussion

Success of this evaluation trial is dependent on the cooperation of centers and staff recruited to the study, and their implementation of the PRSIST Program with high fidelity, and the participation of parents and children from those centers. As such, substantial efforts have been expended in producing informative communication materials and easy-to-use program materials. We believe that the necessary groundwork has been laid, and the next publication on this trial will present results of the efficacy of the PRSIST Program for enhancing children’s self-regulation and related abilities, and educators’ perceived knowledge, attitudes and self-efficacy in supporting children’s self-regulation. The results of this study will provide insight into whether self-regulation benefits can be achieved through low-cost and routine practices, when these are done more intentionally (rather than incidentally), with the aim of maximising self-regulatory challenge and benefit, and in a way that is flexible and compatible with current early-years contexts, practices and routines. If efficacious, this would be a significant departure from many current alternative approaches, which can be difficult to implement with fidelity, and are often costly and time consuming.

